## Abstract

**Background:**

Family-based treatment (FBT) is currently the most effective evidence-based treatment approach for adolescents with anorexia nervosa (AN). Home treatment (HT) as an add-on to FBT (FBT-HT) has been shown to be acceptable, feasible and effective. The described three-arm randomized clinical trial (RCT) is intended to investigate whether FBT-HT demonstrates higher efficacy compared to standard outpatient FBT with supplemental mindfulness-based stress reduction training (FBT-MBSR).

**Methods:**

This RCT compares FBT-HT to standard outpatient FBT and FBT-MBSR as a credible home-based control group in terms of efficacy and delivery. Adolescents with AN or atypical AN disorder (*n* = 90) and their parent(s)/caregiver(s) are to be randomly assigned to either FBT, FBT-HT or FBT-MBSR groups. Eating disorder diagnosis and symptomatology are to be assessed by eating disorder professionals using standardized questionnaires and diagnostic instruments (Eating Disorder Examination, Eating Disorder Inventory, Body Mass Index). In addition, parents and caregivers independently provide information on eating behavior, intrafamily communication, stress experience and weight. The therapeutic process of the three treatments is to be measured and assessed among both participants and care providers. The feasibility, acceptability and appropriateness can thus also be evaluated.

**Discussion:**

We hypothesize that FBT-HT will be an acceptable, appropriate and feasible intervention and, importantly, will outperform both established FBT and FBT-MBSR in improving adolescent weight and negative eating habits. Secondary outcome measures include the reduction in the stress experienced by caregivers, as well as the regulation of perceived expressed emotions within the family, while the intrafamily relationships are hypothesized to mediate/moderate the effectiveness of FBT. The proposed study has the potential to enhance the scientific and clinical understanding of the efficacy of FBT for AN, including whether the addition of HT to FBT versus another home-based adjunct intervention improves treatment outcomes. Furthermore, the study aligns with public health priorities to optimize the outcomes of evidence-based treatments and integrate the community setting.

*Trial registration* This study is registered at ClinicalTrials.gov (NCT05418075).

## Introduction

Anorexia nervosa (AN) is a severe disorder with high morbidity, chronicity and mortality rates [15] associated with substantial suffering on personal, familial and social levels [33, 35]. Recent systematic reviews indicate that parental involvement through family-based treatment (FBT), especially in younger adolescents (12–15 years), is currently the most evidence-based treatment approach for adolescents with AN. [8, 16, 20, 38]. FBT is a well-established treatment modality that aims to normalize adolescents’ weight and eating behaviors [14] by empowering parents as supportive caregivers [11]. Notably, approximately 40–50% of adolescents participating in FBT show complete and stable remission in long-term follow-up studies, meaning that a substantial proportion of patients is still not making sufficient therapeutic progress [25]. Moreover, families with strong parental emotionality show even worse outcomes with FBT [1]. Accordingly, a better understanding of the moderators and mediators of FBT's treatment effects is needed to determine what additional therapies should potentially be offered when standard treatment is not sufficient [20]. In addition, FBT is generally seldom integrated into clinical practice and therapeutic settings [28]. Family and work commitments of parents are reported as common reasons for therapists’ reluctancy to involve parents in treatment [19].

Outreach services generally offer greater flexibility in terms of time and location, enabling the support of family structures in their ordinary environment, which minimizes the burden on all family members [6]. Such services are generally used to intensify treatment during a severe course of illness [24] and, in treatment for eating disorders, to prevent inpatient hospital admissions [30]. Transferring treatment strategies to the home setting is the key challenge to achieving sustained symptom reversal and long-term success in childhood and adolescent mental health treatment [36]. Specifically for adolescents with eating disorders, incorporating home treatment (HT) has been shown to be feasible and acceptable [9, 17], with a significant increase in treatment effects [30]. FBT is particularly well suited as a supplement to HT because the specific eating situations observed in FBT as possible maintaining factors [10] require effective management in the home setting. A recent qualitative study examined parents’ experiences and perceived stress in the context of FBT treatment and symptom persistence in their child [37]. HT could be a supportive element to reassure parents in their tasks prescribed in the FBT sessions and help the family to (re-)establish more beneficial and supportive interactions.

As postulated by Omer and London [29], the therapeutic relationship is the most important factor for therapeutic success. Although several HT programs for adolescents with psychiatric disorders have been developed and evaluated as effective [2, 24], to date, no studies have been able to demonstrate that the greater effectiveness of home-based care was not simply owing to the more intense therapeutic relationship, which may result from the additional time spent with the patient or the greater intimacy of the therapy environment.

The purpose of the proposed study (randomized clinical trial) is to compare the three outpatient treatments (FBT, FBT-HT, FBT-MBSR) for adolescents with AN. We hypothesize that FBT-HT is acceptable, appropriate and feasible and, importantly, outperforms both established FBT alone and FBT supplemented with mindfulness-based stress reduction training (FBT-MBSR) in terms of adolescent weight gain and eating disorder psychopathology. Our primary endpoint is remission of AN symptoms, defined as an increase in body weight as measured by BMI, and a decrease in eating disorder pathology as measured by the Eating Disorder Examination (EDE) total score and EDI-2 total score. Secondary endpoints include stabilization of somatic health status, as measured by vital signs, as well as an improvement in psychosocial well-being and reduction in perceived stress. We hypothesize that FBT-HT will lead to stress reduction in caregivers as well as improvement in interfamily relationships and regulation of perceived and expressed emotions within the family. In addition, we expect that balanced and relaxed family dynamics (integrated in further exploratory analyses as a mediator/moderator variable) will lead to increased effectiveness of FBT and thus improved patient-related outcomes.

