### Measures

Demographic data as well as previous or current psychiatric treatment data will be collected from patients/their parent(s)/caregiver(s). During registration by telephone, patients are to be asked about the required language skills. All measurement instruments (see Table 1) are already digitized and to be electronically transmitted for the study via REDCap, a secure web-based electronic data collection application. The digitized version of the Eating Disorder Examination (EDE) [7] was previously investigated for equivalence with the original face-to-face EDE interview by our group; this study indicated that both instrument versions are overall equivalent in their measured scales, additionally showing that, as a diagnostic tool, the online version is generally answered more honestly [3].

**Table 1 Tab1:** Summary of measures

Construct	Measure	Respondent/format	Time point		
			Week 0	Week 12	12 months
Descriptives	Age, gender, comorbid diagnosis, menstrual status, driven sporting activities, premorbid BMI, medical history	A, C	×		
Primary outcomes	EDE	A_os_	×	×	×
	EDI-2	A_os_	×	×	×
	BMI	A	×	×	×
Secondary outcomes					
Health-related quality of life	KID SCREEN-27	A_os_	×	×	×
Vital parameters	Blood pressure and pulse	A	×	×	×
Expressed emotion	BDSEE	A_os_	×	×	×
Stress perception	PSS-10	C_os_	×	×	×
Mediator/moderator					
Family functions	FB-K	A_o_, C_o_	×	×	×
Exploratory outcome					
Child behavior	CBCL	C_oa_	×	×	×
Implementation characteristics					
Therapy evaluation	FBB	A_o_, C_o_		×	
Process analysis of methods	BPT	A, C, T	Weekly		

*A* adolescent, *C* caregiver, *T* therapist, *o* online, *os* online self-reporting, *oa* caregiver online reporting on adolescent, *BDSEE* Brief Dyadic Scale of Expressed Emotion, *BMI* body mass index, *BPT* Berner Patienten- Therapeutenstundenbogen, *CBCL* child behavior checklist, *ED* eating disorder, *EDE* eating disorder examination, *EDI-2* eating disorder inventory, *FB-K* family questionnaire, *FBB* treatment satisfaction (in German: Fragebogen zur Beurteilung der Behandlung), *PSS* Perceived Stress Scale

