#### Effectiveness

Adolescents’ heights and weights are to be measured to determine BMI at all follow-up timepoints along with an assessment of eating disorder symptoms using the EDE and the Eating Disorder Inventory (EDI-2; [34]). Both instruments have excellent reliability and validity [7, 12]. The primary outcomes for adolescents are improvement in BMI *z*-score based on the CDC growth charts, as well as a decrease in eating-related psychopathology. Secondary endpoints include stabilization of somatic health status, as measured by vital signs (blood pressure and pulse), improvement in psychosocial well-being and reduction in perceived stress. Accordingly, parents will complete the Perceived Stress Scale (PSS; [5]), which is commonly used to quantify subjective feelings of stress. Adolescents will also complete the Brief Dyadic Scale of Expressed Emotion (BDSEE; German translation by [32]), which captures expressed emotions from the patient’s perspective.

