### Data analysis plan

The initial descriptive statistics will summarize participant data characteristics as means, standard deviations, minima, maxima, frequencies and percentages. The validity of stratified randomization will be evaluated by inspecting between-group differences at baseline by means of a one-way analysis of variance (ANOVA), Kruskall–Wallis test or chi-squared test (in dependency of conventional statistical assumptions and the variable type, i.e., continuous versus categorical). Outcome data will be evaluated for the normality assumption by a combination of visual (Q–Q plots, histograms) and statistical (Shapiro–Wilk test) methods and will be transformed if necessary to meet the normality assumption. Participant characteristics of the analyzed sample and dropouts will be subjected to an additional inspection for possible non-random differences. Missing data will be handled by the maximum likelihood estimation method. The effects of the interventions will be assessed as changes in the primary outcomes from pre-test to post-test and follow-up assessment using EDE, EDI-2 and BMI analyzed with a repeated measures ANOVA followed by a post-hoc Tukey’s test to compare treatment means when there is a significant effect. The potential influence of confounding factors (age, premorbid BMI, duration of illness, age at onset, duration and setting of pre-treatment, medication use) will be further explored in sensitivity analyses. The secondary continuous variables will be analyzed in parallel. The measures related to treatment implementation (FBB, BPT) will be evaluated using descriptive statistics. Corrected effect sizes, expressed as Hedges’s *g* and significant deviations beyond the 95% confidence interval, will be computed for between- and within-group terms and will indicate empirical power estimates for a subsequent confirmatory study. Exploratory analyses will test the FB-K measure as a mediator/moderator of efficacy. To examine the FBT process, the ratings of each therapy session by the adolescents and the therapists will be compared and analyzed to assess their common development over time. More advanced statistical methods, such as generalized estimating equations (GEE) (which allow for more flexible modelling of the correlation structure among observations, are less sensitive to violation of assumptions and estimate population-wide average effects) will be also applied to assess differences in BMI percentiles and EDE/EDI-2 trajectories. The statistical significance threshold will be set to *p* < 0.05.

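### The primary endpoint is called remission, but the plan tests three continuous outcomes at p < 0.05 and does not say which must succeed

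*Protocol article*

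**What the plan says.** The Introduction names one primary endpoint: "Our primary endpoint is remission of AN symptoms, defined as an increase in body weight as measured by BMI, and a decrease". The sentence then places that decrease in two instruments, the EDE and the EDI-2, each by its total. No cut-off is given for any component.

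The rest of the article treats the endpoint as several continuous measures:

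- Table 1 (Measures) lists EDE, EDI-2 and BMI under the row label "Primary outcomes".
- The Effectiveness section uses the plural and specifies a standardised BMI: "The primary outcomes for adolescents are improvement in BMI *z*-score based on the CDC growth charts, as well as a decrease in eating-related psychopathology".
- The Data analysis plan evaluates change from baseline at both later visits, "using EDE, EDI-2 and BMI analyzed with a repeated measures ANOVA followed by a post-hoc Tukey’s test to compare treatment means". It contains no remission variable. It adds GEE models for BMI percentiles and for the EDE and EDI-2 trajectories.
- The significance level is fixed once, for everything: "The statistical significance threshold will be set to *p* < 0.05".

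The Power analysis section sizes one group-by-time interaction test (three groups, two time points, f = 0.2, r = 0.5, 80% power, 5% error). It arrives at 66 evaluable participants, raised to 90 for 25% attrition. It does not say which outcome this test concerns.

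**The concern.** The endpoint is defined one way and analysed another. A reader of the Introduction expects a statement about remission, and the Introduction itself uses that word for a patient status when it reports long-term remission rates under FBT. The analysis cannot deliver such a statement.

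With three primary outcomes and one unadjusted threshold, the success criterion is also open. If one significant outcome is enough, the 5% error rate does not describe the primary analysis as a whole. If all are needed, as the conjunction in the Introduction suggests, the 80% power does not describe it either. Left open, the choice can be made after the results are seen.

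**Working it through.** **Inputs.** From the Power analysis section: f = 0.2, r = 0.5, three groups, m = 2 time points, alpha 0.05, 66 evaluable (22 per arm), 25% attrition. From the Data analysis plan: three outcomes, p < 0.05, Tukey's test after a significant effect. Assumed, because the article gives no values: the correlations between outcomes, and f = 0.2 on every outcome.

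**1. The plan's own figure.** For the group-by-time interaction, lambda = f² × N × m / (1 − r), with df 2 and N − 3.

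- N = 66: lambda = 0.04 × 66 × 2 / 0.5 = 10.56; power = 0.818.
- N = 63: power = 0.798. So 66 is the smallest total with equal arms that reaches 80%.
- Attrition: 66 / 0.75 = 88, rounded up to 90.

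The sample size arithmetic is right, for one outcome.

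**2. Success under two possible rules.** With independent outcomes:

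- Any of three: 1 − 0.95³ = 0.143.
- All three: 0.818³ = 0.547.

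For correlated outcomes, 20,000 trials were simulated per setting, with 22 per arm. In the power runs one arm was shifted by 0.849 SD of the change score, which gives the same lambda: 22 × 0.849² × 2/3 ≈ 10.6.

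| Correlation between outcomes | Any of three, no true effect | All three, f = 0.2 on each |
|---|---|---|
| 0 | 14% | 55% |
| 0.3 | 14% | 60% |
| 0.5 | 12% | 63% |
| 0.7 | 11% | 68% |
| 0.9 | 9% | 74% |

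With 0.7 between EDE and EDI-2 and 0.2 between each of them and BMI, the figures are about 12 to 13% and 62%.

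**3. The stated hypothesis.** The Introduction claims that FBT-HT outperforms both other arms. The error rate for that claim is different, because FBT-HT must win both Tukey contrasts on the same outcome after a significant F test.

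- All arms equal: a false double win on any of the three outcomes occurs in about 0.4% of trials.
- Least favourable case (FBT-HT equal to one comparator and far better than the other): about 0.97% per outcome, so at most about 1 − 0.9903³ = 0.029 over three independent outcomes, and less when they are correlated.

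**4. Cost of an adjustment.** At alpha = 0.05 / 3 and N = 66, omnibus power per outcome is 0.675, against 0.818 at 0.05.

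**The case against.** Several arguments on the other side have weight.

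- **The remission label may be only loose wording.** The Introduction explains it at once as directional change in three measures. A reader might infer a responder definition under which any BMI gain with any fall in scores makes a patient remitted. No section states such a rule, so that reading is not supported. The mismatch between label and analysis remains.
- **The error inflation does not reach the main hypothesis.** A reader might infer that a false claim of FBT-HT superiority exceeds 5%. Step 3 shows that it does not. The 9 to 14% applies to finding some difference between some arms on some outcome.
- **Power for the full hypothesis is lower still, but not mainly because of the three outcomes.** Beating both arms by Tukey on all three outcomes has about 22% power at correlations 0.7 and 0.2. Yet beating both on one outcome alone has only about 51%, because the trial is sized for the omnibus test. The 22% should not be charged to this point.
- **GEE as a second route to success** is not stated. The article says only that GEE will also be applied.
- **A multiplicity rule can sit in an analysis plan that is not shown**, and the article mentions a later confirmatory study. The absence of a rule alone would therefore be no finding. What stands is that the published text contradicts itself on what the primary endpoint is, while fixing one threshold and one power figure for it.

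Separate tests per outcome are an inference, but no multivariate or composite test is named, so it is the plain reading.

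**Conclusion.** The point holds as an internal contradiction with a limited numerical consequence. The primary endpoint is labelled remission, no remission status is analysed, and three continuous outcomes share an unadjusted threshold. The 5% and 80% cannot both describe this primary analysis:

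- if any one outcome suffices, the omnibus error rate is about 9 to 14%;
- if all three are required, omnibus power with 66 completers is about 55 to 74%.

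These ranges rest on assumed correlations from 0 to 0.9, and the power range also on f = 0.2 for each outcome. The calculation of 66 and 90 is correct for one outcome, and a false claim that FBT-HT beats both arms stays at or below about 3%.

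**What to change.** - In the Introduction, replace remission with the outcomes actually analysed: change in BMI z-score, EDE total and EDI-2 total. No remission claim is then made. Use the same BMI measure in the Data analysis plan.
- Name week 12 as the primary time point, which fits the two-time-point power calculation. Label the 12-month and GEE results as secondary or sensitivity.
- Pre-specify one multiplicity rule across the three outcomes, for example a fixed sequence at 0.05, or Holm. The order of a sequence is the sponsor's choice. It should be justified with regard to the eligibility of patients with atypical AN and unremarkable BMI, who may have less weight to regain.
- State that the group-by-time interaction F test opens each step, followed by Tukey contrasts of FBT-HT against each comparator.
- State that the 80% power applies to the omnibus test on one outcome.

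The cost is wording, with no extra patients under a fixed sequence. The downside of a sequence is that later outcomes can be claimed only if the earlier ones succeed. Holm avoids an order but lowers per-outcome omnibus power, to about 67% at its strictest step with 66 completers.

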## Methods

### Participants

Participants are to include a consecutive sample of 90 adolescents (aged 12–18 years) with full-syndrome AN or atypical AN (as well as their caregivers) that have been referred to the outpatient eating disorders unit at the Department of Child and Adolescent Psychiatry of the University Psychiatric Hospital, Zurich, Switzerland. Only patients with atypical AN who have all psychopathological symptoms of AN but whose percent mean body mass index (BMI) is clinically unremarkable according to the Centers for Disease Control and Prevention (CDC) growth charts [23] will be included in this study. Participants will be randomly assigned to one of three treatments (FBT, FBT-HT, FBT-MBSR). The inclusion criteria are as follows: (1) living with at least one adult caregiver,(2) willingness and ability to engage in family therapy; (3) being medically stable for outpatient treatment, as determined by a physician; (4) lack of comorbidities that contraindicate psychotherapy (e.g., psychosis); (5) an IQ greater than 75 (as determined by testing/clinical impression by a professional); (6) adequate German language skills; (7) residency within the Canton of Zurich, as outreach services necessary for two of the treatment groups are limited to this geographical region.

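### The primary BMI outcome has no single scale, and in a sample mixing AN with atypical AN of unremarkable BMI, neither diagnosis nor the baseline outcome value is a listed covariate

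*Protocol article*

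**What the plan says.** **Population.** The Participants section plans "a consecutive sample of 90 adolescents (aged 12–18 years) with full-syndrome AN or atypical AN". Atypical cases are those with "all psychopathological symptoms of AN but whose percent mean body mass index (BMI) is clinically unremarkable". No expected share of atypical AN and no cap on it is given.

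**Endpoint.** The Introduction states: "Our primary endpoint is remission of AN symptoms, defined as an increase in body weight as measured by BMI", together with lower EDE and EDI-2 totals. There is no separate weight rule for atypical AN.

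**Scale of BMI.** The Introduction, the primary-outcome rows of Table 1 and the ANOVA sentence of the Data analysis plan say BMI without a scale. The Effectiveness section says: "The primary outcomes for adolescents are improvement in BMI *z*-score based on the CDC growth charts". The GEE sentence of the Data analysis plan refers to "differences in BMI percentiles and EDE/EDI-2 trajectories".

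**Covariates and strata.** The Data analysis plan lists six factors for sensitivity analyses: age, premorbid BMI, illness duration, age at onset, prior treatment (duration and setting) and medication. Diagnosis and the baseline value of the outcome are not among them. On allocation it says: "The validity of stratified randomization will be evaluated by inspecting between-group differences at baseline". The stratification factors are not named.

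**The concern.** A primary outcome needs one scale. In patients aged 12 to 18 followed to 12 months, unstandardised BMI mixes growth with treatment response. A z-score removes the age and sex reference. A percentile is a non-linear transform of the z-score, flat in the tails and steep in the middle. The entry criteria spread this sample from underweight to unremarkable BMI, so the choice of scale also decides whose change counts most. If the scale is left open, it can be settled after the results are seen.

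The mixed population adds a second problem. Patients who enter underweight and patients who enter with an unremarkable BMI may well change by different amounts. With about 30 per arm, the arms can differ by chance in their share of atypical AN. If diagnosis and baseline value are outside the model, that imbalance moves the estimate and the explainable variance stays in the error term.

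**Working it through.** **1. Reproduce the plan's own figure.** Inputs from the Power analysis section: f = 0.2, alpha 0.05, r = 0.5, k = 3 groups, m = 2 time points, N = 66, group-by-time interaction.

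- Noncentrality: λ = f²·N·m/(1 − r) = 0.04 × 66 × 2/0.5 = 10.56.
- Degrees of freedom: (k − 1)(m − 1) = 2 and (N − k)(m − 1) = 63.
- Power = 0.818. The smallest N for 80% is 64, or 66 in equal arms.
- Attrition: 66/0.75 = 88, which the protocol rounds up to 90.

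The sample-size arithmetic is sound under its own inputs.

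**2. How far the scales differ.** With Φ the standard normal distribution function:

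- z from −3 to −2: Φ(−2) − Φ(−3) = 0.0228 − 0.0013 = 0.021, about 2 percentile points.
- z from −0.5 to +0.5: Φ(0.5) − Φ(−0.5) = 0.383, about 38 percentile points.

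The same one-unit gain in z thus counts about 18 times as much in mid-range as in the tail (0.383/0.021). The z-values are illustrations; the protocol gives no baseline distribution.

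**3. What baseline adjustment gains.** With two time points, the group-by-time test compares change scores. Assume equal variance σ² at both times.

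- Change score: residual variance 2σ²(1 − r) = σ² at r = 0.5.
- Follow-up adjusted for baseline: σ²(1 − r²) = 0.75σ².
- Ratio: (1 − r²)/[2(1 − r)] = (1 + r)/2 = 0.75, a 25% reduction.
- λ becomes 10.56/0.75 = 14.08. Power is 0.917 with 62 error degrees of freedom (baseline only) and 0.916 with 60 (two further terms).

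The gain depends on r. At an assumed r = 0.8 the ratio is 0.90, a 10% reduction.

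**4. What adding diagnosis does.** Let q be the share of atypical AN and D the difference in mean BMI change between diagnoses, in SDs of change. Leaving diagnosis out inflates the variance by 1 + q(1 − q)D². For q from 0.1 to 0.5 (assumed), power at N = 66 falls from 0.818 to 0.793–0.809 at D = 0.5, and to 0.721–0.782 at D = 1.0.

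**5. Chance imbalance.** With 30 per arm and an assumed q = 0.3, the difference in atypical share between two arms has SD √(2 × 0.3 × 0.7/30) = 0.118, about 12 percentage points.

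**6. Dilution, under assumptions only.** If atypical patients had no between-arm BMI effect, and f = 0.2 described full-syndrome AN alone, the pooled effect would be 0.2(1 − q). Power at 66 would be 0.726, 0.617, 0.498 and 0.381 for q = 0.1, 0.2, 0.3 and 0.4. Neither condition, nor q, is in the documents.

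**The case against.** **On scale.** The article never says raw BMI. BMI may simply name the measure, with the Effectiveness section supplying the metric, and the GEE analysis is additional to the ANOVA. This is a fair reading and reduces part of the point to wording. It does not remove the conflict: the ANOVA sentence leaves the scale open, and the GEE is stated on percentiles, which weight this sample very differently.

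**On baseline.** Repeated measures ANOVA already includes the pre-test value and removes level differences between diagnoses. That is correct. Baseline adjustment is a gain in precision, not the repair of an invalid test, and the plan reaches its 80% without it.

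**On stratification.** A reader might infer that allocation ignores diagnosis. The documents do not support this: randomisation is called stratified, and diagnosis may be one of the unnamed factors. A condensed article may leave those names to the full protocol.

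**On dilution.** A reader might infer from the figures in step 6 that the trial is underpowered for BMI. That needs a known share of atypical AN, a zero effect in that group and f = 0.2 read as the full-syndrome effect. The Power analysis section does not limit f to full-syndrome AN; if f already describes the mixed sample, there is no fall. The protocol also does not say that weight gain is irrelevant to recovery in atypical AN. EDE and EDI-2 apply to both groups in any case.

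**On restricting the weight claim to full-syndrome AN.** At q = 0.3 this leaves about 46 of 66 completers and power of about 0.65 at f = 0.2. The pooled analysis has 0.82 if atypical patients respond equally and 0.67 if they have half the effect (f = 0.2 × 0.85 = 0.17). Restriction wins only when the effect in atypical AN is close to zero, so the pooled estimate should stay primary.

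**On the baseline tests.** Significance tests cannot validate a randomisation, but these change no outcome estimate and carry no weight here.

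**Conclusion.** The point holds as an inconsistency in a primary outcome and an avoidable loss of precision. BMI is stated without a scale in three places, as a z-score in one and as percentiles in another. A sample that is heterogeneous by design is analysed with neither diagnosis nor the baseline outcome value as a listed covariate.

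Baseline adjustment is worth about 10 points of power (0.82 to 0.92 at 66 completers). This rests on the protocol's f = 0.2 and r = 0.5 and on equal variances over time; the variance saving is smaller if r is higher. Diagnosis adds roughly 1 to 10 points more in the scenarios of step 4, which rest on assumed shares and differences. That gain may overlap with baseline adjustment for BMI, because entry BMI separates the two diagnoses.

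Dilution of the BMI effect by atypical AN is possible, but the documents give no basis for its size, and adjustment would not remove it. The change should be made, but nothing here shows the design or the sample size to be wrong.

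**What to change.** 1. Name the CDC BMI z-score of the Effectiveness section as the only BMI metric in the Introduction, Table 1, the primary analysis and the GEE analysis.
2. For each primary outcome, analyse follow-up values adjusted for the baseline value of that outcome, diagnosis (AN versus atypical AN) and the stratification factors actually used.
3. Report the BMI effect by diagnosis, with the arm-by-diagnosis interaction, as a supportive analysis. Keep the pooled estimate primary.

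The cost is wording and a few error degrees of freedom (63 to about 60 at 66 completers, or slightly fewer depending on the number of strata). No new data are needed, since diagnosis and baseline values are collected at entry. The diagnosis-specific estimates will be imprecise and should be presented as such. All of this should be fixed before outcome data are examined by arm.
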